### Concealment mechanism {16b}

Only the (PI) will know what code corresponds to which treatment arm. Trial randomization codes will be kept on a password-protected Excel sheet located on a secure server to which only the PI will have access to.

### Implementation {16c}

Trained research assistants will enroll participants. Once a patient has been successfully screened, a binary code that is to be allocated to each participant will be generated. Participants will be assigned to interventions based on whichever binary code they are allocated.

## Assignment of interventions: blinding

### Who will be blinded {17a}

Since this is a prospective, randomized, open-label, blinded endpoint trial all outcomes will be adjudicated in a blinded fashion to preserve impartiality. All operators performing CT or echocardiographic analysis will be blinded to study group allocation at the time of image acquisition. Imaging will be assessed off-line in a blinded manner. This level of blinding is maintained throughout the conduct of the trial, and only when the data has been analyzed according to statistical analysis plan, and conclusions regarding the primary and secondary outcomes are made, will the associated personnel be unblinded. Even though the adjudication of clinical events in the safety composite is blinded, we cannot exclude that bias may be introduced by the trial staff when filling the case report files. Data monitoring will be performed to minimize this.

### Procedure for unblinding if needed {17b}

Not applicable since this is an open-label trial.

## Data collection and management

### Plans for assessment and collection of outcomes {18a}

After signing the informed consent and inclusion into the study, patients’ baseline data will be collected, including medical history and concomitant medication. Data from echocardiograms obtained before and after AVR will be collected. Data on adverse clinical events and study protocol adherence during the treatment period will be collected through telephone interviews at 1 and 2 months following randomization. Three months following randomization, all study outcomes will be assessed. Patients will be invited for an on-site clinical visit. The visit will include an extensive interview to assess for any potential clinical, adverse event, hospital or emergency room visits, or bleeding events that might have occurred during the study period. Reports from any hospital or emergency room visits will be obtained and analyzed. During the same visit a cardiac CT and echocardiography will be performed (Fig. 3).

#### Computed tomography

Computed tomography examination will be performed 90 ± 5 days from the moment of randomization on a 128-layer CT device with intravenous administration of iodine contrast medium and synchronization of the recording with the ECG. The previously described CT acquisition protocol will be employed [20]. Briefly, image contrast medium, 80–100 mL, will be administered intravenously through an intravenous cannula at least 20 gauge wide at a rate of 4–6 mL/s. For the optimal representation of the leaflets, imaging will be performed throughout the entire cardiac cycle without radiation dose modulation, with image reconstruction every 5% R-R interval (20 separate phases) with a slice thickness of 0.6 mm. In most patients, an X-ray tube voltage of 100–120 kV will be used, exceptionally 140 kV for extremely obese patients or patients with pacemakers. To achieve an optimal pulse rate during imaging (< 70/min.), if necessary, patients will be premedicated with beta-blockers and/or ivabradine. Imaging will begin when the contrast agent density in the ascending aorta reaches 300 Hounsfield units, and the imaging field will be limited to the heart area.

Hypo-attenuated leaflet thickening is identified by a contrast CT of the heart as an increased thickness of the bioprosthetic leaflet. A typical thickening assumes a meniscus-shaped configuration. The thickening begins and is thickest at the point of insertion of the leaflet for the valve frame and gradually narrows towards the free edge of the leaflet. The extent of HALT is assessed by a semiquantitative scale for each leaflet separately. The percentage of leaflet involvement is estimated starting from the leaflet base. The assessment is performed using multiplanar reconstructions.

The advantage of CT is its high spatial resolution. Sometimes, the assessment of HALT can be limited by artifacts caused by the valve stent frame, motion artifact, or suboptimal contrast, making the computed tomography study insufficient for diagnosis. Leaflet restriction caused by HALT can be described as RLM. However, due to the limited temporal resolution of CT of the heart, RLM should be investigated only in cases of a diagnosis of HALT. Otherwise, the probability of a false positive diagnosis increases. In the literature, HALT and RLM are used mainly as synonyms for subclinical (latent) leaflet thrombosis of bioprosthetic heart valves. The extent of HALT will be described per leaflet, using a 4-tier semiquantitative grading scale as described previously [20]. Grade 3 or higher will be considered HALT positive valve for the purpose of this study. Similarly, in the presence of HALT, the extent of RLM will be assessed per leaflet on multiplanar reformatted and 4D volume rendered images, using a 4-tier semiquantitative grading [20].

A specialist radiologist will evaluate the degree of HALT and RLM by analyzing a contrast enhanced CT study of the heart. The radiologist will be blinded to the patient’s pharmacotherapy or to which group the patient has been randomized.

#### Echocardiography

Echocardiography is a widely accessible and validated method of assessing bioprosthetic valve function. An echocardiographic examination will be performed on two occasions during the study. The first one will be done during the index hospitalization, after AVR prior to discharge. It will assess for the definition of successful aortic valve replacement. The second echocardiographic examination will be done 90 ± 5 days after randomization. Repeated echocardiograms at baseline and at 3 months will determine the degree of hemodynamic valve deterioration as suggested in VARC-3 [18]. All echocardiograms will be blindly adjudicated at a core lab.

Echocardiographic examinations will be based on transthoracic echocardiography (TTE) and guidelines for echocardiographic assessment of prosthetic valves [22]. Transthoracic echocardiography is the gold standard in assessing the hemodynamic characteristics of bioprosthetic heart valves. It follows the same principles as for native heart valves although it has some peculiarities. Two-dimensional TTE will be used as the first line of imaging, and three-dimensional transesophageal echocardiography (TEE) will be performed in cases of bioprosthetic dysfunction. Comprehensive echocardiographic imaging of a prosthetic valve involves the use of multiplanar views with care to confirm appropriate leaflet morphology and motion and to identify the presence of calcifications or structural abnormalities of any component of the prosthesis.

Transthoracic echocardiography Doppler imaging will be performed at an imaging speed of 100 mm/s. The parameters that will be recorded are the bioprosthetic aortic valve mean gradient and the effective orifice area (EOA). Measurements will be performed during two cardiac cycles in sinus rhythm. In the case of atrial fibrillation, Doppler measurements will be performed during the period of physiological heart rate and through five cycles. For EOA calculations, the continuity equation obtained from the stroke volume will be used. It is recommended to adjust the cycle length to 10%. Doppler imaging will be done during quiet breathing or in the middle of expiratory apnea.

Color Doppler will show the presence of pathological intra- and/or paravalvular regurgitation blood flows, if any. The search will be performed in multiple sequences with appropriate setting (Nyquist limit around 50–60 cm/s). Accurate localization of paravalvular regurgitation can be challenging. In this case, TEE is necessary to assess the localization and degree of regurgitation.

### Plans to promote participant retention and complete follow-up {18b}

Participants will be provided the medication, clinic visit, echocardiography, and CT at no additional costs. Participants will be thoroughly educated about the risks and benefits of the study drugs. All medical procedures will be performed by trained clinical staff. Participants will be encouraged to communicate with research staff via telephone regarding any problems or irregularities. Adherence to protocol involves attending the clinical visit and taking at least 90% of their medication. During the week of the scheduled visit, a “no-show” will lead to three attempts to reschedule a participant’s visit. Medication compliance will be evaluated by counting returned tablets.

### Data management {19}

The data collection plan for this study is to utilize a database to capture all treatment and adverse event data for all enrolled subjects.

### Confidentiality {27}

Identifying information of the participating patients will be removed and substituted with a study participant number. All data will be de-identified. Nonetheless, we will maintain a file that links subject name with the study participant number thereby enabling us to locate the study participant’s research record if needed. Data will be analyzed in aggregate only, and no identities will be revealed. It will be specifically used for the purposes outlined in this proposal and not for any other purpose. Study documentation will be stored in a secure location until the end of the study and all data analyses are complete. At that time, all study material will be placed in a secured long-term storage facility until it is deemed appropriate to destroy the study material.

### Plans for collection, laboratory evaluation, and storage of biological specimens for genetic or molecular analysis in this trial/future use {33}

Not applicable. No genetic or molecular analysis were planned in the study protocol.

## Statistical methods

### Statistical methods for primary and secondary outcomes {20a}

The primary outcome will be tested using the chi-square test of proportions. It will be tested for superiority using a 2-sided chi-square test at the 0.05 significance level in the intention-to-treat population. The secondary outcome will be test for non-inferiority with a single comparison between the study groups of the secondary outcome measure (safety composite) per-protocol. To test for noninferiority, we determined whether the upper boundary of the 95% confidence interval for the difference in the rate of secondary outcome measure between the treatment group and the control group was less than or equal to the prespecified noninferiority margin of 5 percentage points. If this requirement for noninferiority will be met, testing for the superiority of the safety composite will be performed at a two-sided alpha level of 0.05. The Kolmogorov-Smirnov test will be used to test normality of distribution for continuous data. For exploratory outcome measures, between-group differences will be analyzed using independent samples *t*-tests, chi-square test, or Mann-Whitney tests, where appropriate. If necessary, multivariable regression analysis will be used to adjust for imbalances in main prognostic variables between the intervention and control groups. Time-to-event analysis for the safety composite outcome and its components will be performed. Cumulative event-free survival will be estimated by Kaplan-Meier analysis.

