### Intervention description {11a}

All eligible patients must provide written, informed consent before randomization to antithrombotic treatment with either apixaban for 3 months followed by ASA indefinitely (intervention) or to ASA indefinitely (control). Randomization is performed in a 1:1 ratio.

Patients randomized to the intervention arm will receive an open-label anti-Xa type DOAC, apixaban without addition of an antiplatelet drug. The treatment will be initiated on the fifth postoperative day. Planned postoperative invasive procedures (such as pacemaker implantation) would temporarily delay commencement of apixaban, which would then be continued for 3 months. Thereafter, treatment will be converted to ASA 100 mg daily indefinitely. The dosing of apixaban follows standard clinical practice for anticoagulation. The standard dose of apixaban is 5 mg twice daily. The dose should be reduced to 2.5 mg twice daily if 2 or more of the following criteria are present: (1) age ≥ 80 years, (2) body weight ≤ 60 kg, (3) serum creatinine ≥ 1.5 mg/dL (133 μmol/L).

Patients assigned to the control arm will receive an open-label ASA 100 mg per day. The treatment will be initiated on the fifth postoperative day and continued indefinitely. The current standard dosing of ASA is 75–100 mg daily. There are no additional dose adjustments for ASA. In patients who are intolerant to ASA, conversion to 75 mg of clopidogrel a day will be recommended. Medication compliance will be self-reported by trial participants, resembling clinical practice.

Antithrombotic therapy based on the study protocol will start at the time of randomization which will be on the fifth postoperative day. Patients participating in the study should take the study drug according to the study protocol every day for a period of 90 days. Prior to randomization, starting from the first postoperative day, antithrombotic therapy with low molecular weight heparin (e.g., enoxaparin, dalteparin, or fondaparinux) will be employed without addition of antiplatelet or oral anticoagulant medications.

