### Criteria for discontinuing or modifying allocated interventions {11b}

Patients randomized to the control arm who develop an indication for anticoagulation (e.g., atrial fibrillation) during follow-up will cross over to the apixaban group. Conversely, patients in the intervention group who develop an indication for antiplatelet therapy (e.g., percutaneous coronary intervention) will cross over to the ASA group. All patients will remain as originally allocated for the intention-to-treat analysis of initial strategy. Per-protocol analysis will be performed for safety composite outcomes.

An investigator may withdraw a participant from the study for the following reasons: (1) significant study intervention non-compliance; (2) identification of a clinical adverse event, laboratory abnormality, or other medical condition which could harm the patient in any way by continued participation in the study; (3) if the participant meets an exclusion criterion that precludes further participation; (4) participant requests withdrawal from the trial.

In case of an overt valve thrombosis, ischemic stroke, or systemic embolism before the end of the study, patients will be managed according to the best standards of care regardless of the study protocol allocation. Additional cardiac imaging including a heart ultrasound (transthoracic and/or transesophageal) and, if necessary, a cardiac CT will be considered. The result of this additional imaging as well as previous imaging exams of the heart will be available to the treating physician for evaluation and decision on the appropriate antithrombotic treatment. If necessary, the study drug will be stopped and anticoagulant therapy with unfractionated heparin and/or a VKA will be introduced. On the other hand, if an overt Valve Academic Research Consortium 3 (VARC-3) Type 2–4 bleeding event [18] occurs, the study drug will be discontinued. In any case, immediate medical care, and treatment, including hospitalization will be available.

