### Strategies to improve adherence to interventions {11c}

Adherence to protocol will be indicated by attending all the scheduled visits, conducting the telephone interviews, and undergoing planned echocardiographic and cardiac CT imaging as well as taking at least 95% of their medication. Several consecutive attempts during the week of the scheduled visit will be made to reschedule a participant’s visit. Medication compliance will be evaluated by counting returned tablets; participants will be asked to bring their medication at every visit. Participants will also be asked if there was any difficulty in adhering to the medication taking during each visit or telephone interview.

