### Methods in analysis to handle protocol non-adherence and any statistical methods to handle missing data {20c}

Study population will be randomized to the intervention (apixaban) or the control (ASA) arm. Carefully selected patients based on the inclusion/exclusion criteria will provide a basis for a steady protocol adherence. In 5% of patients, a protocol violation, loss to follow-up, and withdrawal of consent are anticipated. All patients will remain in their originally allocated arm for the intention-to-treat analysis of all outcomes. Exploratory analyses will include a per-protocol analysis, which will include only patients who received their randomly assigned treatment, and an as-treated analysis in which we will compare patients who received apixaban with those who received aspirin with multivariable adjustment for imbalances in baseline characteristics. Maximal efforts to reduce the missing data to a minimum will be employed. Missing data will be handled via multiple imputations in statistical analyses.

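### The analysis set for the safety non-inferiority test is stated two ways, and one reading of the per-protocol set would remove patients taken off drug for a type 2–4 bleed

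*Protocol article*

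**What the plan says.** All references are to the protocol article.

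- **Statistical methods {20a}**, on the safety composite: "The secondary outcome will be test for non-inferiority with a single comparison between the study groups of the secondary outcome measure (safety composite) per-protocol". Non-inferiority is met if the upper 95% confidence limit for the difference in rates is at most 5 percentage points. If it is met, superiority of the same composite is tested at two-sided 0.05, with no analysis set named for that step.
- **Discontinuing or modifying interventions {11b}** also assigns the safety composite to a per-protocol analysis. It describes crossover in both directions and says that if a VARC-3 type 2–4 bleed "occurs, the study drug will be discontinued".
- **Non-adherence and missing data {20c}**: "All patients will remain in their originally allocated arm for the intention-to-treat analysis of all outcomes". The next sentence reads: "Exploratory analyses will include a per-protocol analysis, which will include only patients who received their randomly assigned treatment".
- **Adherence {11c}** describes protocol adherence as attending visits, interviews and imaging, "as well as taking at least 95% of their medication". **Retention {18b}** describes it as "attending the clinical visit and taking at least 90% of their medication".
- **Secondary outcome measures** define the composite as VARC-3 bleeding of every type, myocardial infarction, stroke and death from any cause at 3 months.

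**The concern.** One analysis cannot be both the single governing comparison and an exploratory one. Because {20a} and {20c} disagree, the set that decides the safety claim could be chosen after the data are seen, in a trial where treatment is open-label. The superiority step inherits the problem. Read straight on from {20a}, it would run in the per-protocol set, where randomisation no longer protects the comparison.

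The choice matters because study drug is stopped after the more serious bleeds, and those bleeds count towards the composite. A per-protocol set that depends on how much drug was taken can therefore lose patients because they had the outcome. If such bleeds are more common on apixaban, that loss pushes the result towards non-inferiority.

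**Working it through.** **1. The plan's own figures.** The article gives no sample size, power or expected rate for the safety composite. Its 158 evaluable and 166 randomised patients relate to HALT. They reproduce: 30% versus 12% with 79 per arm gives 79.9% power, and 158 × 1.05 = 165.9, so 166. They do not bear on this point, except that 166/2 = 83 per arm is used below.

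**2. The sections side by side.**

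| Section | Set for the safety composite | Status |
|---|---|---|
| {20a} | per-protocol | the single non-inferiority comparison |
| {11b} | per-protocol | planned |
| {20c} | intention-to-treat, as for every outcome | per-protocol listed as exploratory |

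No sentence ranks them.

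**3. Who could leave a per-protocol set.** Treatment lasts 90 days ({11a}).

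- 95% rule: 0.95 × 90 = 85.5 days. A permanent stop before about day 86 fails.
- 90% rule: 0.90 × 90 = 81 days. A permanent stop before about day 81 fails.
- Type 1 bleeds carry no instruction to stop drug, so those patients stay.
- Under the literal {20c} wording, a patient who began the assigned drug and later bled can also stay.

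**4. Size, if bleeders are dropped (all rates assumed).** The {20a} rule is to declare non-inferiority if

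(pA − pC) + 1.96 × √[pA(1 − pA)/nA + pC(1 − pC)/nC] ≤ 0.05.

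Let t be the type 2–4 bleed rate, t1 the type 1 rate, o the rate of other composite events (at most one event per patient), and f the fraction of type 2–4 bleeders removed. The expected rate in an arm of the per-protocol set is

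[t1 + o + t(1 − f)] / (1 − t·f).

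Take t = 7% on apixaban and 2% on aspirin, with t1 = 5% and o = 2% in both arms:

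- f = 0: 14% − 9% = 5.0 points, exactly the margin.
- f = 0.5: 0.105/0.965 − 0.080/0.990 = 10.9% − 8.1% = 2.8 points.
- f = 0.95: 0.0735/0.9335 − 0.0710/0.9810 = 7.9% − 7.2% = 0.6 points.

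Chance of declaring non-inferiority with 83 randomised per arm and t = 7% versus 2% (200,000 simulated trials per cell; exact enumeration agrees within 0.2 points):

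| t1 / o | Intention-to-treat | Half dropped | 95% dropped |
|---|---|---|---|
| 2% / 1% | 3.6% | 12.4% | 40.8% |
| 3% / 2% | 3.0% | 9.3% | 26.5% |
| 5% / 2% | 2.7% | 8.0% | 19.8% |
| 10% / 3% | 2.6% | 5.8% | 11.9% |

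With a true 8-point excess (t = 10% versus 2%, t1 = 5%, o = 2%), the figures are 0.6%, 3.7% and 17%. If nobody is dropped (f = 0), the two sets give the same result. If type 2–4 bleeds are equally common in both arms, dropping them leaves the expected difference at zero, so the bias needs an imbalance.

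**The case against.** The strongest reply is that the article never ties the 95% or 90% threshold to the per-protocol set. Those figures sit in sections on adherence and retention. The only definition of the set is the one in {20c}, and a patient who started the allocated drug and then bled can satisfy it. Stopping drug after a type 2–4 bleed is what the protocol instructs, so it is not obviously a deviation. Whether the stop is permanent is not stated either. All of this stands. A reader might infer that the per-protocol set does drop the patients who bleed. The text supports that only conditionally, and never for type 1 bleeds.

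A second reply is that {20c} promises an intention-to-treat analysis of every outcome, so the safety composite would be reported both ways and detailed membership can be left to the analysis plan. The first part is fair: what is missing is the hierarchy. The second does not remove the problem, because the article does not leave the governing set open. It fixes it twice, differently.

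Third, intention-to-treat is not neutral for non-inferiority here. Control patients who come to need anticoagulation cross over to apixaban, which can pull the arms together. This stands and is the reason to keep a per-protocol analysis alongside.

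A reader might also see a contradiction between {11a}, "Medication compliance will be self-reported by trial participants, resembling clinical practice", and the tablet counts elsewhere. The two can complement each other, since patients report remaining tablets by telephone and tablets are counted at the visit. The point does not rest on it.

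**Conclusion.** The contradiction over the analysis set is certain from the text and affects the trial's only formal safety conclusion. {20a} and {11b} say per-protocol, {20c} says intention-to-treat with per-protocol exploratory, and the superiority step has no set of its own. The two adherence thresholds also conflict.

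Removal of bleeders is a conditional risk. It arises if an adherence threshold defines the per-protocol set and the drug stop is permanent, and it then affects only type 2–4 bleeds early enough to breach the threshold. Its size cannot be taken from the document. With assumed type 2–4 bleed rates of 2% versus 7%, where the true excess equals the margin, the chance of a non-inferiority claim rises from about 3–4% to 6–12% if half of those bleeders are dropped, and to 12–41% if 95% are. It does not rise if none are dropped. The HALT analysis, set as intention-to-treat in {20a}, is unaffected.

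**What to change.** Reconcile {11b}, {20a} and {20c} so that they say the same thing:

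1. The safety composite is analysed in all randomised patients by allocated arm, with events after drug stop counted. This set governs the non-inferiority conclusion.
2. The per-protocol analysis is a required supporting analysis, reported alongside because crossover can narrow the intention-to-treat difference.
3. Superiority of the composite is tested in the intention-to-treat set only.
4. The per-protocol set is defined once, with one adherence threshold in place of the two in {11c} and {18b}. Stopping study drug because of a composite event never excludes the patient or that event.

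This changes wording only. It adds no patients or visits and leaves the treatment and stopping rules as they are. The cost is some dilution of the intention-to-treat comparison by crossover, which item 2 is there to expose.
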